### Data Analysis

Quantitative statistical data analysis will be conducted using Stata SE 16.0 (StataCorp). For each group, we will test using an intent-to-treat model to determine the effectiveness of each group on (1) social and emotional mindsets and skills outcomes (curiosity, generosity, persistence, purpose, growth mindset, and prosocial behavior) and (2) gender norms, attitudes, and beliefs. Descriptive statistics will be calculated for each measure per intervention group and will be used to check for skewness and data non-normality. The psychometric properties of each measure will be assessed using confirmatory factor analysis to assess the adequacy of factor structures suggested by previous studies. Additional analyses will be conducted using *t* tests and logistic regressions to explore potential confounders of these relationships such as age, gender, and assigned facilitator. Validated measures will be used for structural equation modelling to test the relationships between intervention groups on social, emotional, and identity learning measures. For each model tested, structural equation modelling will be used to test (1) overall fit, (2) the significance of structural paths, and (3) the amount of variability of the latent variables accounted for by observed variables. Model fit will be assessed by using goodness-of-fit indices including the chi-square, the root mean square error of approximation [41], the comparative fit index [42], the Tucker-Lewis index [43], and the standardized root mean residual.

Qualitative data analysis will be conducted in ATLAS.ti (ATLAS.ti Scientific Software Development GmbH). After completion of interviews and focus groups, a Tanzanian translator will complete translation from Swahili to English. The translations will be cross-checked by researchers in Tanzania. Transcripts will be coded using grounded theory methodology, and content analysis will be performed to identify key themes. Quotes will be selected as exemplars of these themes. Additional qualitative materials include participant observations, facilitator debrief reflections, parent session notes, and teacher interviews. Each of these documents will be translated from Swahili to English by the research team and summarized, and key themes will be extracted. Artifacts from youth will be collected throughout the intervention implementation to serve as exemplars of curriculum implementation.

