### Research Team Training

Core research team members will complete training on research ethics prior to the study. Their training will include confidential handling of data, obtaining consent and assent from study participants, and data collection and management. The field research team will be composed of 2 master trainers and 12 community facilitators. Training will be conducted in two phases. First, the master trainers will be trained over two weeks by the *Discover* Project Manager. The training will cover research ethics, gender-transformative content, technology use, and partnering with the community. Second, community facilitators will be trained with support from the master trainers over eight days. During the training, 6 facilitation principles will be adapted to facilitate discovery learning. They are (1) scaffolding learning to create a safe space for learners, (2) emphasis on learning over education, (3) withholding judgment since learning is a nonlinear process, (4) encouraging teamwork and positive group dynamics, (5) disrupting gender norms, and (6) encouraging a growth mindset. Sessions will use a combination of presentations, discussion, practice, and reflection.

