### Participant Recruitment and Eligibility Criteria

Participants will be recruited from four primary schools from low-income urban neighborhoods of Temeke District. They will be selected based on the following criteria: (1) the school should not have had an intervention within the last 7 years that included a behavior change component, a teachers’ capacity-building component on soft skills (eg, positive discipline or facilitation skills), or a gender equity program; (2) the school should be a public/government school; (3) the school should have a large enough number of early adolescents to obtain the sample size required for study; and (4) the school should be representative of an average school in Tanzania in terms of socioeconomic status, religion, amenities, etc. Participants will be eligible if they meet the following criteria: (1) they must be a 10- to 11-year-old student in Grade 3, 4 or 5 in the 4 selected study sites; (2) they must verbally assent to participate in the study; and (3) their caregiver must provide consent for them to participate in the study. The after-school intervention will be conducted with a total of 579 youth. Students will be randomized into Groups A, B, and C. Figure 1 provides an overview of the scheduling of the intervention and research elements. A complete checklist listing the items to address in a trial protocol according to the CONSORT (Consolidated Standards of Reporting Trials) guidelines can be found in Multimedia Appendix 2 [33].

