### Randomization Procedure

Participating 10- to 11-year-olds from grades 3, 4, and 5 will be identified from each school. At each school, we will hold an event where we line up eligible youth outside their classrooms. A research assistant will hold a box with pencil sharpeners of different colors inside. The box will have a small hole large enough to fit a hand through but small enough that students cannot see the pencil sharpeners. Each youth will select one sharpener at random. Students will be assigned to groups A, B, or C depending on whether they pick pink, yellow, or blue pencil sharpeners, respectively. Youth will then be matched to their selected pencil sharpener with a research assistant holding the same color, and that research assistant will register students to the assigned group. Table 1 lists the expected results of randomization to the three groups, according to the sample size calculation, and the intervention components that will be administered to each group.

**Table 1 table1:** Intervention components offered per study arm.

Study components	Group A (n=186)	Group B (n=185)	Group C (n=208)
Number of sessions	6	6	18
Ubongo Kids videos	✓	✓	✓
Mixed gender groups of size	15-26	4-5	4-5
Discussion and activities	✗	Self-guided	Guided by trained facilitators
Parent-child workbook	✗	✗	✓

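### Assigned facilitator is listed as a potential confounder in the additional analyses, but it is part of how the randomised arm is delivered and belongs in the model as a clustering factor

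*Protocol article*

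**What the plan says.** The Data Analysis section gives the effectiveness test first: "we will test using an intent-to-treat model to determine the effectiveness of each group". No facilitator term is attached to it. A later sentence begins "Additional analyses will be conducted using *t* tests and logistic regressions", and the stated purpose of those analyses is to "explore potential confounders of these relationships such as age, gender, and assigned facilitator". The relationships are most naturally read as those between study group and outcome.

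Three other places bear on this:

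- **Randomization Procedure.** Arm is fixed child by child: "Each youth will select one sharpener at random", and the colour determines Group A, B or C.
- **Table 1.** In the row on discussion and activities, Group A has none, Group B is self-guided and Group C is "Guided by trained facilitators".
- **Research Team Training.** The field team has "2 master trainers and 12 community facilitators". The article does not say which arms they staff, or when and how a child is assigned to one.

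**The concern.** Age and gender are fixed before the draw. They can be unbalanced by chance, and adjusting for them leaves the treatment comparison intact. A facilitator who guides a child's sessions because that child drew Group C is a consequence of the allocation. Such a variable cannot confound the randomised comparison, and adjusting for it can absorb the very contrast under study.

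In Table 1, facilitator guidance is what separates C from B in the discussion row, and identifying effective components is a stated secondary aim. At stake is an adjusted result, reported beside the intent-to-treat result, that cannot be estimated or that answers a different question without saying so. Facilitator also has a real role that the confounder label hides: children who share a facilitator may have correlated outcomes, and the standard error should reflect that.

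**Working it through.** The plan gives no figure on this point to reproduce. The check is whether the arm contrasts can be estimated once facilitator is in the model.

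**Inputs from the article.** Arms of 186 (A), 185 (B) and 208 (C), total 579 (Table 1); 12 community facilitators (Research Team Training).

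**Assumptions.** Facilitators carry equal loads, so 208/12 = 17.3 children each if all 12 work only in C. Outcomes have a within-group SD of 1. For the simulation (2000 runs), the true C effect is 0.28 SD and the between-facilitator SD is 0.2. The staffing pattern is unknown, so several are shown.

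**Step 1: estimability.** The linear predictor is intercept + arm B + arm C + facilitator indicators. The algebra is the same for linear and logistic regression.

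| Staffing and coding | Columns | Rank | C−A estimable | C−B estimable |
|---|---|---|---|---|
| Only in C; A and B coded as none | 15 | 14 | no | no |
| Only in C; A and B share the reference level with one facilitator | 14 | 14 | yes, for that facilitator only | yes, for that facilitator only |
| In B and C; A coded as none | 15 | 14 | no | yes |
| All 12 in A, B and C, balanced | 14 | 14 | yes | yes |

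In the first row the 12 facilitator indicators add up to the Group C indicator, so the model cannot separate the two. The second row is what remains if one facilitator indicator is dropped to make the model run.

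**Step 2: what the C coefficient means.**

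- *Only in C, reference-facilitator coding.* The C coefficient compares one facilitator's children with Group A. Its variance is 1/17.3 + 1/186 + 0.2² = 0.0578 + 0.0054 + 0.0400 = 0.1032, so its SE is 0.32. The simulation gave 0.317, against 0.119 for the C−A estimate without facilitator terms.
- *All arms, balanced.* Simulated mean 0.283 and SE 0.103, with and without facilitator in the model.

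**Step 3: facilitator as a clustering factor.** If all 12 work only in C:

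- SE of C−A ignoring facilitator: √(1/208 + 1/186) = √0.01018 = 0.101.
- SE with facilitator variance included: √(0.01018 + 0.2²/12) = √(0.01018 + 0.00333) = √0.01351 = 0.116, close to the simulated 0.119.

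Under these assumptions the standard error that ignores facilitator is too small by a factor of 0.116/0.101 = 1.15. This is where facilitator legitimately enters. The 0.2 is illustrative, since the article gives no between-facilitator variance.

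**The case against.** The strongest reply is that little depends on this sentence. The effectiveness test is intent-to-treat, and facilitator appears only in additional analyses that explore. That stands: the main contrast is neither lost nor altered. Table 1 also says who guides discussion and not who staffs sessions. Groups A and B attend six sessions each, and somebody must run them. If the same facilitators cover all arms in balance, adjustment is harmless. That stands too. Interest in facilitator differences also fits the aim of identifying effective components.

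Three stronger readings are tempting, and the article does not support them.

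- *A reader might infer that the plan removes or un-identifies the treatment effect.* This needs facilitators confined to C (or, for C−A, to B and C) and applies only to the additional analysis.
- *A reader might infer a large loss of precision.* With 12 facilitators all in C and facilitator variance left out, one facilitator's children against Group A give √(1/17.3 + 1/186) = 0.251 and a one-sided minimum detectable effect of 2.4865 × 0.251 = 0.62. The arithmetic is right, but it describes one coefficient read in isolation under a worst case. In the same fitted model, the child-weighted average over facilitators against A keeps the SE of 0.101, so no information is lost.
- *A reader might infer that covariates will be chosen by testing them on trial data.* The text says explore. It does not say that these tests select covariates for the effect model, and covariate detail may sit in a fuller document.

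What the reply does not rescue is the label. Even with facilitators in every arm, facilitator is a delivery and clustering factor.

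**Conclusion.** The point holds as a misclassification in the additional analyses. Assigned facilitator should not stand beside age and gender as a potential confounder of a comparison set by an individual draw. The stated intent-to-treat comparison is unaffected.

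The size depends on staffing. With facilitators only in C, the adjusted C−A and C−B contrasts are inestimable or become one-facilitator effects. With facilitators in B and C, adjusted C−A is lost and C−B remains. With balanced staffing of all arms, nothing changes. Two things are inferred: that facilitators are assigned after the draw, which is the natural reading for guidance given only to Group C but is not stated, and that the relationships in question are those between group and outcome. This is a worthwhile correction to a secondary analysis and does not threaten the trial's main result.

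**What to change.** 1. Remove assigned facilitator from the list of potential confounders.
2. Limit adjustment to variables fixed before the draw, for example school, sex, age and baseline score.
3. State which arms the 12 community facilitators staff, and how children are assigned to them.
4. Treat facilitator as a clustering factor, with a random effect in the arm or arms that facilitators staff, so that the standard errors reflect it.
5. Report between-facilitator variation as an implementation result. This preserves the interest in facilitator differences.

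The cost is a change of wording and model specification. No new data are needed beyond the record of which facilitator each child had, which the planned analysis already presumes. The article reports that data analysis was not concluded at the time of writing, so the change could still be made then.

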### Availability of Data and Materials

The data sets that will be generated or analyzed during this study will not be made publicly available due to the sensitive age of the study participants (10- to 11-year-olds) at baseline but may be available from the corresponding author on reasonable request. The author will vet requests to be certain that appropriate institutional review board (IRB) approvals and data safety guidelines are in place before distribution.

## Results

This project was funded in November 2016 by the Bill and Melinda Gates Foundation. The University of California, Berkeley Committee for Protection of Human Subjects IRB approved this study (CPHS Protocol Number: 2017-01-9464; date: July 11, 2019). The primary local partner, Health for a Prosperous Nation, obtained ethical clearance for these research activities from the National Institute of Medical Research, the local IRB in Tanzania (Ref. NIMR/HQ/R.8a/Vol. IX/ 2491; date: May 15, 2019). In addition, the project sought and secured support from all local partners, Temeke Municipal Council and the Ministry of Education in Tanzania. Screening and enrolment of participants was done in June 2019. Data for the baseline survey was collected in July 2019.

The first phase of the intervention was delivered starting in the month of July 2019 for a period of 6 weeks to 579 participating 10- to 11-year-olds. Throughout the course of the intervention, systematic observations were carried out. Follow-up data was collected in the months of October and November 2019. The first phase of the intervention closed out in November 2019. At the time of writing this paper, data analysis had not yet been concluded. The second phase of the intervention kicked off with enrolment of participants in July 2020. This phase of the study targets the same participants from phase I and expects to reach 500 participants. The baseline survey will be conducted from August to September 2020. The intervention will be delivered remotely via technology for ten weeks from September 2019. The key findings from this phase of the project and the longitudinal data collected will be submitted for publication in peer-reviewed literature and presented at national and international conferences.

## Discussion

Findings from *Discover* will provide evidence of the impact of the different components of a developmentally informed social, emotional, and identity learning intervention for very young adolescents by comparing outcomes in groups A, B, and C and emergent themes from interviews and focus groups. Synthesis of quantitative and qualitative results will allow for identification of the highest impact components and resources required for the intervention. Results from structural equation modelling will be used to create a testable model of the relationships between social, emotional, and identity development on gender equity outcomes. These results will be used to develop a scalable, low-resource intervention program. This study tests the translation of developmental science principles to youth programs. In addition, findings have the potential to be replicated in other low-resource contexts. This study has some limitations. Randomization of adolescents will be done at the individual level and not the school level to maximize participation. Findings from the intervention will therefore apply to the individual level but cannot be extrapolated to the community level. Despite efforts to ensure intervention groups receive the package of components pertinent to that group, there is a possibility that some adolescents will discuss their group’s activities with friends and siblings, and therefore groups may become aware of intervention components received by other groups. The findings from this study will contribute to the evidence base on development science for very young adolescents. Further, the study design, methods, and evaluation will be useful for other studies that are invested in gender-transformative interventions through support of social and emotional learning. *Discover* will identify the impact of different intervention components that can be leveraged to replicate and scale up similar programs in peri-urban, low-resource settings.

## Appendix

Multimedia Appendix 1 Social emotional mindsets and skills targeted by Discover.

Multimedia Appendix 2 CONSORT Checklist.

Multimedia Appendix 3 Measurement scales used in Discover.

## Abbreviations

CONSORT: Consolidated Standards of Reporting Trials
IRB: institutional review board
